## **2. Study objective**

### **2.1 Primary objective**

The primary outcome is POAF in 6 days, defined as a supraventricular arrhythmia lasting for >30 seconds. Patients will be monitored continuously beginning within one hour after the surgery to the 6th day postoperatively through the NS-SP-B-01 Attached Dynamic ECG Recording System. In addition, the overall lasting time of supraventricular arrhythmia will also be recorded for evaluating AF burden. Heart

rates will be continuously monitored, including lowest/highest/average heart beats, premature atrial/ventricular contractions etc. Two independent and blinded research doctors will interpret the ECG and determine the existence of POAF.

## **2.2 Secondary objectives**

### **2.2.1 Safety assessments**

- 1) The incidence of transferring to on-pump CABG intraoperatively;
- 2) The need for blood transfusion;
- 3) Re-operation for postoperative bleeding caused by partial cardiac denervation procedure;
- 4) The incidence of epicardial effusion within 30 days after discharge;
- 5) Arrhythmias other than AF within 30 days after discharge;

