## **3.2 Eligibility criteria**

We will consecutively recruit adult patients who are undergoing CABG (on-pump/off-pump) and agree to participate in this clinical trial.

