#### **3.6.2 Blinding**

As different surgical operations are involved, complete double-blindness cannot be achieved. In order to reduce the researcher bias, surgeons are not allowed to know the result of patient's assignment until surgery, and the third-party supervisor responsible

for randomization shall inform the surgeons of the results only after general anesthesia and before the surgical procedure starts. Patients and data analysts will be blinded throughout the process. Unblinding will be done under the third-party supervision after all data analysis is completed.

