### **4.2 Baseline comparability of randomized groups**

Demographic and clinical characteristics of patients at baseline will be presented by randomised group. Number of subjects, mean, standard deviation, median, interquartile range (IQR), minimum, and maximum will be used for description of continuous variables. Continuous variables will be tested by Student's t test if normally distributed; otherwise, by the Mann-Whitney U test. Counts and percentages will be used to summarize the categorical variables. Chi-squared test or Fisher's exact test will be applied for categorical variables, as appropriate.

Intraoperative data such as number of grafts, % off pump, % saphenous vein/radial artery, duration of operation will also be presented.

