### **5.2 Safety**

In the analysis of safety/harms patients will be analysed both by ITT and according to the operation received (i.e. per-protocol). Only patients who received the surgical procedure to which they were randomly allocated will be included in the per protocol analysis of safety data.

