## **8. Statistical test for secondary endpoints**

### **8.1 Statistical analysis method**

Secondary outcomes including safety and economics will also be analyzed according to approach mentioned in 4.2. Unless otherwise stated, statistical significance level is set to 0.05 (2-sided).

For clinical concerns, the incidence of epicardial effusion within 30 days after discharge and arrhythmias other than AF within 30 days after discharge will be analysed as delayed epicardial effusion and critical arrhythmias, respectively. Delayed epicardial effusion was defined as new-onset epicardial effusion (moderate or more) within 30 days after discharge. Critical arrhythmias other than AF was defined as arrhythmias requiring immediate clinical intervention, such as complete atrioventricular block.

Since POAF happens after surgery and has a effect on postoperative clinical events, we think the analysis of all cost during hospitalization may not be appropriate. Only postoperative cost for each patient will be included in the final analysis. Similarly, only postoperative length of hospitalization will be included in the final analysis.

Although the follow-up visit of 30 days is relative short, we intend to compare the MACCE outcome between the 2 groups in the final manuscript.

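### The conversion-to-on-pump outcome cannot count a planned off-pump patient who is started on-pump after the allocation is known, because the planned pump strategy is not recorded beforehand

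*Supplement*

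**What the plan says.** The latest SAP and protocol version 2.0 agree on the following.

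- **Outcome.** Item 1 under 2.2.1 Safety assessments is "The incidence of transferring to on-pump CABG intraoperatively". Neither document defines a transfer or states a denominator.
- **Population.** SAP 3.2 recruits "adult patients who are undergoing CABG (on-pump/off-pump) and agree to participate in this clinical trial".
- **Analysis.** SAP 5.2 analyses safety by intention to treat and per protocol. SAP 8.1 states: "Secondary outcomes including safety and economics will also be analyzed according to approach mentioned in 4.2". That means a chi-squared or Fisher's exact test by arm. SAP 8.1 refines the effusion, arrhythmia, cost and length-of-stay outcomes but does not mention conversion.
- **Disclosure.** Under SAP 3.6.2 the third-party supervisor is to "inform the surgeons of the results only after general anesthesia and before the surgical procedure starts".
- **Pump strategy.** It is not among the minimisation factors listed in SAP 3.6.1, nor among the baseline items in protocol 6.2. Protocol 6.3 collects bypass and cross-clamp times. SAP 4.2 presents "Intraoperative data such as number of grafts, % off pump", as a description.
- **Procedure.** SAP 3.4 describes on-pump denervation under extracorporeal circulation. Off-pump, fat-pad resection during the operation depends on tolerance and stable hemodynamics. Failing that, denervation follows completion of the grafts.

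**The concern.** Two separate things are at issue.

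First, a patient planned for on-pump surgery cannot convert. With everyone randomised in the denominator, the reported rate understates the risk for the patients who can have the event.

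Second, and more important, the surgeon knows the arm before bypass could begin, and the procedure is described differently for the two pump strategies. If knowledge of the allocation led a surgeon to start a planned off-pump patient on-pump, that patient would be logged as an on-pump case. The outcome counts only a change made during the operation, so the extra use of bypass would not enter it. Such a patient also can no longer convert, which slightly lowers the count in the denervation arm. The outcome could then look neutral or favourable while bypass use against plan was higher. With no plan on record, this could not be reconstructed reliably afterwards.

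**Working it through.** The documents give no expected conversion rate, no off-pump share and no rate of changed plans, so there is no stated figure to reproduce. The only input from the plan is 215 patients per arm (SAP 3.5). Everything else below is an assumption shown over a range.

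**1. Effect of the all-patient denominator.** Let *s* be the planned off-pump share and *c* the conversion rate among planned off-pump patients. The all-patient rate is *s* × *c*. Take *c* = 5% in control and 10% with denervation, with a two-sided level of 0.05 and normal-approximation power.

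| *s* | All-patient rates | Risk difference (points) | Power, all 215 per arm | Power, planned off-pump only |
|---|---|---|---|---|
| 30% | 1.5% vs 3.0% | 1.5 | 0.181 | 0.187 |
| 50% | 2.5% vs 5.0% | 2.5 | 0.275 | 0.285 |
| 70% | 3.5% vs 7.0% | 3.5 | 0.369 | 0.375 |

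The risk difference among planned off-pump patients is 5.0 points. The risk ratio is 2 in every row, and power hardly moves. The denominator affects interpretation of the absolute risk, not the validity of the comparison.

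**2. Effect of an uncounted on-pump start.** Take *s* = 50%, so 215 × 0.5 = 107.5 planned off-pump patients per arm, and *c* = 5% in both arms. Let *q* be the share of planned off-pump denervation patients started on-pump because of the allocation.

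- Counted conversions, control: 107.5 × 0.05 = 5.4.
- Counted conversions, denervation: 107.5 × (1 − *q*) × 0.05.
- Any bypass use among planned off-pump denervation patients: *b* = *q* + (1 − *q*) × 0.05. Control: 5.0%.
- Off-pump percentage among all patients: 0.5 × (1 − *b*). Control: 0.5 × 0.95 = 47.5%.

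| *q* | Conversions counted, control vs denervation | Bypass use among planned off-pump | Off-pump percentage, all patients |
|---|---|---|---|
| 5% | 5.4 vs 5.1 | 5.0% vs 9.8% | 47.5% vs 45.1% |
| 10% | 5.4 vs 4.8 | 5.0% vs 14.5% | 47.5% vs 42.8% |
| 20% | 5.4 vs 4.3 | 5.0% vs 24.0% | 47.5% vs 38.0% |

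**3. Would the descriptive off-pump percentage reveal it?** With half the patients planned off-pump and 215 per arm, chance imbalance in the planned share has a standard error of about √(2 × 0.25 / 215) = 4.8 points. At *q* = 10% the off-pump percentage differs by 47.5 − 42.75 = 4.75 points, about one standard error. At *q* = 20% it differs by 9.5 points, about two.

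Among planned off-pump patients at *q* = 10%, bypass use differs by 14.5 − 5.0 = 9.5 points. Its standard error is √(0.05 × 0.95 / 107.5 + 0.145 × 0.855 / 107.5) = 4.0 points, so the difference is about 2.4 standard errors. The same shift is much easier to see once the plan is on record.

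**4. Would restricting to patients who started off-pump suffice?** At *q* = 10% that gives 5.4/107.5 = 5.0% against 4.84/96.75 = 5.0%. It still misses the on-pump starts, and it selects on a choice made after allocation. The restriction has to be on the recorded plan.

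**The case against.** The case on the other side is substantial, and most of it stands.

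- **The denominator.** A reader might infer that including planned on-pump patients biases the result or costs power. Step 1 shows that it does neither. The all-patient denominator also follows from the general analysis rules and the absence of a restriction; it is not written out for this outcome.
- **Visibility.** A reader might infer that extra bypass use would be invisible. It would not be: bypass time is collected for each patient and the off-pump percentage is presented. A large shift would show there. A modest one could not be told from chance imbalance in planned strategy.
- **Mechanism.** A reader might infer that denervation will push surgeons to start on-pump. Nothing in the documents says so. SAP 3.4 estimates 5 minutes of added surgery and provides for denervation after the grafts when it is not tolerated earlier, which may make a change of plan less likely. The risks listed in SAP 1.4 are longer operation, blood loss and arrhythmia, not use of bypass, so the documents give no basis for calling it the likeliest harm.
- **Importance.** This is one of several secondary safety outcomes, and the trial is not powered for it.

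What remains is that the outcome as defined cannot count an allocation-driven on-pump start, and without the recorded plan no other planned analysis can relate actual pump use to what was intended.

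**Conclusion.** The point holds as a possible bias that the outcome cannot detect, not as a demonstrated one. Including planned on-pump patients multiplies the absolute rates and the risk difference by the off-pump share (0.3 to 0.7 over the assumed range) and leaves the between-arm comparison sound. The weakness that matters is disclosure of the allocation before the procedure with no prior record of the pump plan.

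Under the moderate illustration, the counted conversions slightly favour denervation while bypass use against plan is nearly three times as high (14.5 / 5.0 = 2.9). That result is driven by the assumed 10% rate of changed plans, for which the documents give no evidence either way; at zero the problem disappears. The primary POAF analysis is not affected. This is a cheap improvement to a secondary safety outcome.

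**What to change.** - Add a case report form field for the planned pump strategy, completed before the allocation is disclosed.
- In SAP 2.2.1 and 8.1, define the outcome as any use of cardiopulmonary bypass, whether an on-pump start or a conversion, among patients whose recorded plan was off-pump, compared by randomised arm. Conversions during the operation can still be reported as a component.
- Tabulate planned against actual pump use by arm.

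The cost is one extra field, a few lines of SAP text and a smaller denominator for this outcome. Surgeons put a plan on paper but remain free to depart from it. Sample size and the primary analysis do not change. The field has to be in place prospectively, since a plan written down after disclosure would not serve.

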### **3. Study plan and procedures**

#### **3.1 Overall study design and participants' timeline**

**Figure 1** shows the SPIRIT (Standard Protocol Items: Recommendations for Interventional Trials) guidelines  instructing the designation of our study.

|                                              | STUDY PERIOD            |                |                 |                                     |                               |
|----------------------------------------------|-------------------------|----------------|-----------------|-------------------------------------|-------------------------------|
|                                              | Enrolment               | Allocation     | Post-allocation |                                     |                               |
| TIMEPOINT                                    | Pre Intervention | T 0 | Surgery  | Post-operative Hospital stay | Follow-up Clinic Visit |
| ENROLMENT:                            |                         |                |                 |                                     |                               |
| Eligibility screen                           | X                       |                |                 |                                     |                               |
| Informed consent                             | X                       |                |                 |                                     |                               |
| Allocation                                   |                         | X              |                 |                                     |                               |
| INTERVENTIONS:                        |                         |                |                 |                                     |                               |
| Control(no intervention)              |                         |                | X               |                                     |                               |
| Cardiac denervation                   |                         |                | X               |                                     |                               |
| ASSESSMENTS:                          |                         |                |                 |                                     |                               |

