## **1.4 Benefit /risk and ethical assessment**

The intervention group will receive additional partial cardiac denervation procedure, namely cutting off the LOM and resecting the fat pad along the Waterston groove. Potential risks are as follows: extending operation time, increasing intraoperative blood loss and postoperative arrhythmias. The related technique has been applied in surgical treatment of AF and proved to be safe and feasible. The surgery will remove only part of the CANS and will not affect the patient's normal sinus rhythm. All the participants can contact the the study physician who will help them to get the right medical treatment, if any suspected arrhythmias-related adverse events emerge after surgery. The study will be approved by the Institutional Review Board of Fuwai Hospital.

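### The re-operation safety item counts only bleeding attributed to denervation, so as worded it cannot be compared between the arms

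*Supplement*

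**What the plan says.** The third safety outcome has the same wording in protocol 2.2.1 and SAP 2.2.1: "Re-operation for postoperative bleeding caused by partial cardiac denervation procedure".

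Only one arm has that procedure. Section 1.4 of both documents states "The intervention group will receive additional partial cardiac denervation procedure", and the schedule in protocol 3.1 lists the other arm as "Control(no intervention").

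SAP 8.1 sets the analysis: "Secondary outcomes including safety and economics will also be analyzed according to approach mentioned in 4.2". SAP 4.2 supplies the test: "Chi-squared test or Fisher's exact test will be applied for categorical variables, as appropriate". In SAP 8.1 the "statistical significance level is set to 0.05 (2-sided"). SAP 5.2 names two analysis sets: "In the analysis of safety/harms patients will be analysed both by ITT and according to the operation received (i.e. per-protocol"). It limits the per-protocol safety set to patients who had the procedure they were allocated.

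SAP 8.1 redefines or narrows effusion, other arrhythmias, cost and length of stay. It leaves the re-operation item alone.

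Elsewhere the protocol carries no causal limit. The schedule in 3.1 has a plain re-operation row, and 6.3 collects any secondary operation.

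On blinding, SAP 3.6.2 says "As different surgical operations are involved, complete double-blindness cannot be achieved". Surgeons learn the allocation once the patient is under anaesthesia. Blinded assessment is described for the ECG reading (section 2.1), but not for re-operation.

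**The concern.** A randomised comparison shows whether an added procedure causes more returns to theatre without anyone having to judge the cause of each one. Item 3 puts that judgement inside the outcome. A control patient taken back for bleeding does not count. An intervention patient taken back for the same kind of bleeding counts only if someone decides that the denervation caused it.

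The planned test then sets attributed cases against a near-structural zero, and it can mislead in either direction. A real excess disappears if the bleeding is put down to other sites. An apparent excess arises if background bleeding in the intervention arm is put down to denervation. No rule in the documents protects that decision. Item 3 is also the only re-operation outcome on the list.

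**Working it through.** **Inputs.** 215 patients per arm (SAP 3.5, protocol 8.2), two-sided 0.05 (SAP 8.1), chi-squared or Fisher (SAP 4.2). The documents give no re-operation rate, so there is no plan figure to reproduce. The rates of 1% to 5% below are assumptions.

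**Step 1: who can have the event.** In the per-protocol safety set nobody in the control arm has been denervated, so the count is 0 by definition. Under ITT it is 0 unless a control patient received denervation.

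**Step 2: what the test responds to.** With equal arms and all *k* events in one arm, the two-sided Fisher p-value is 2 × C(215, *k*) / C(430, *k*).

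- *k* = 4: 2 × (215/430)(214/429)(213/428)(212/427) = 0.123
- *k* = 5: multiply by 211/426, giving 0.061
- *k* = 6: multiply by 210/425, giving 0.030

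Six attributed cases are significant and five are not. Control-arm bleeding does not enter the calculation. Expected events per arm are *k*/2, that is 2 to 3, so Fisher is the conventional choice. An uncorrected chi-squared test would already cross 0.05 at four cases (p = 0.0445).

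**Step 3: how far attribution drives the result.** Suppose the true rate *r* of re-operation for bleeding is the same in both arms, and a share *f* of intervention-arm cases is attributed to denervation. Attributed cases then follow Binomial(215, *r* × *f*), and the harm signal needs at least 6:

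| Assumed rate *r* | Expected cases (215 × *r*) | *f* = 1 | *f* = 0.5 | *f* = 0.25 |
|---|---|---|---|---|
| 1% | 2.15 | 2.2% | 0.1% | 0.0% |
| 2% | 4.30 | 26.2% | 2.2% | 0.1% |
| 3% | 6.45 | 62.7% | 10.7% | 0.6% |
| 4% | 8.60 | 86.3% | 26.2% | 2.2% |
| 5% | 10.75 | 96.0% | 45.0% | 5.5% |

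There is no true excess in any cell. At 3%, the chance of declaring harm runs from 0.6% to 62.7% on the attribution share alone.

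**Step 4: the same test on an unrestricted outcome.** Count every re-operation for bleeding in both arms and use Fisher at 215 per arm:

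- Equal true rates of 2%, 3% or 5%: false-positive rate 1.8%, 2.3% or 3.0%, so the test is valid.
- A doubling from 2%, 3% or 5%: power about 14%, 25% or 44%, so the test is weak.
- Precision at 3% in both arms: 1.96 × √(2 × 0.03 × 0.97 / 215) = 1.96 × 0.0165, about ±3.2 percentage points by the simple normal approximation. That interval can be interpreted, even though a p-value alone would say little.

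**The case against.** The case against making much of this has several parts.

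- **Bleeding is measured elsewhere.** A reader might infer that the plan has no valid comparison of bleeding at all. That goes too far. The need for transfusion (item 2) has no causal limit and is compared between the arms. Adverse events are recorded whether or not they are thought related (protocol 7.1). SAEs are notified to the data monitoring committee (protocol 9). Transfusion does not measure return to theatre, however, so the gap in item 3 remains.
- **The data are not lost.** A reader might infer that control-arm re-operations are thrown away. They are collected (protocol 6.3 and the schedule) and are left out only of this endpoint. But no text says that the unqualified count will be the one compared.
- **Who attributes is not stated.** It is tempting to say that the unblinded surgical team will decide. The documents establish only that surgeons know the allocation. They do not name who judges the cause. The supportable point is the missing rule and the absence of described blinded adjudication.
- **The named risk is different.** Section 1.4 names intraoperative blood loss. Postoperative bleeding that needs re-operation is related, but is not what is named there.
- **The high error rates are conditional.** They need most cases to be attributed. With a quarter attributed, the chance of a signal is at most 5.5% over the assumed rates. If six patients truly bled from the denervation sites, the signal is real harm. This is fair, but it does not rescue the test. With perfect attribution a single case already shows harm and a test against zero adds nothing. With imperfect attribution the test measures the attribution.

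**Conclusion.** The point holds for this one item. As worded, it is not comparable between the arms: the control count is zero by definition in the per-protocol safety set, and zero under ITT apart from crossovers. The claim that it is strictly zero in every analysis is not supported. Significance turns on whether six rather than five intervention-arm cases are attributed to denervation (p = 0.030 against 0.061). Those p-values rest only on 215 per arm, a control count of zero and Fisher's test. The error rates and power figures also rest on assumed background rates of 1% to 5%, and the error rates on assumed attribution shares.

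The item also disagrees with the protocol's own schedule and data collection list, which carry no causal limit. If an all-cause comparison is what the sponsor intends, the documents need to be aligned.

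Severity is moderate. This is one of five secondary safety items, no decision rule is tied to it, and the primary endpoint and sample size are untouched.

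**What to change.** 1. In section 2.2.1 of both documents, drop the causal clause and define item 3 as any re-operation for postoperative bleeding, counted in the same way in both arms.
2. In SAP 8.1, make ITT the main analysis of this item. Report the counts by arm and the risk difference with a 95% confidence interval, and state that power is low.
3. Record the reason for re-operation and the bleeding site in the case report form. Present denervation-site bleeding as a descriptive listing without a test.

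The cost is a wording change in two documents and at most a field or two for reason and site. Secondary operations are already collected in protocol 6.3, so no new visit, patient or procedure is needed. The change makes the comparison interpretable but does not make it powerful.
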